## Abstract

**Background:**

Patients with mental disorders have a higher prevalence of sleep problems than the general population. Sleep problems may include insomnia, circadian rhythm disorders, or hypersomnia. A transdiagnostic approach combining cognitive behavioral therapy for insomnia (CBT-I) with chronotherapy addressing a broad range of sleep problems has shown promising results in a limited number of studies. The aim of the study is to investigate the efficacy of a transdiagnostic sleep intervention for patients with sleep problems comorbid to bipolar disorder, unipolar depression, or attention deficit disorders. The primary hypothesis is that the intervention improves sleep quality compared with a control group. The secondary hypotheses are that the intervention increases subjective and objective sleep efficiency, reduces sleep onset latency, wake after sleep onset, number of awakenings, and severity of insomnia; and that it improves well-being, personal recovery, work ability, and consumption of sleep medication compared with a control group.

**Methods:**

The study is a randomized controlled trial enrolling 88 outpatients with bipolar disorder, major depression, or attention deficit disorder with symptoms of various sleep problems (insomnia, circadian rhythm disorders, or hypersomnia). Patients are allocated to either an intervention group receiving six sessions of transdiagnostic sleep treatment or to a control group receiving a single session of sleep hygiene education. Assessments are made at baseline, at week two, and after 6 weeks in both groups. Actigraphy is performed continuously throughout the 6-week study period for all patients. The primary outcome is changes in the subjective appraisal of sleep quality (Pittsburgh Sleep Quality Index). The secondary outcomes are changes in sleep efficiency, sleep onset latency, wake after sleep onset, number of nocturnal awakenings (based on actigraph and sleep diary data), changes in insomnia severity (Insomnia Severity Index), well-being (WHO-5 Well-Being Index), personal recovery (INSPIRE-O), work ability (Work Ability Index), and consumption of sleep medication (sleep-diaries).

**Discussion:**

The study was initiated in 2022 and the inclusion period will continue until mid-2024. The results may have implications for the development and implementation of additional treatment options for patients with mental disorders and comorbid sleep problems.

**Trial registration:**

ClinicalTrials.gov. NCT05406414. Registered on June 6, 2022.

**Supplementary Information:**

The online version contains supplementary material available at 10.1186/s13063-024-07903-6.

## Administrative information

Note: the numbers in curly brackets in this protocol refer to SPIRIT checklist item numbers. The order of the items has been modified to group similar items (see http://www.equator-network.org/reporting-guidelines/spirit-2013-statement-defining-standard-protocol-items-for-clinical-trials/).

## Introduction

### Background and rationale {6a}

The estimated prevalence of chronic insomnia falls in the 10–20% range in the general population [1], and chronic insomnia is associated with increased risk of cardiovascular disease [2], diabetes [3], impaired quality of life [4], increased suicidal ideation [5], increased risk of depression [6], and impaired work functioning [7]. Insomnia often presents as comorbidity to a mental disorder. Regardless of psychiatric diagnoses, insomnia is found in nearly 50% of patients [8], and the incidence of low sleep quality is even higher, close to 90%, for patients with depression [9]. Apart from insomnia, circadian rhythm disorders, hypersomnia, and insufficient sleep hygiene practices may affect sleep [10].

Circadian rhythm disorders with a preference for later bedtime are common in patients with unipolar depression (UD) [11], bipolar disorder (BD) [12], and attention deficit disorders (ADHD) [13]. Patients tend to go to bed later than 2am and sleep during the daytime, resulting in a delayed or irregular sleep phase causing social jetlag [10]. Misalignment with the light/dark cycle and hypersomnia are common problems in patients with BD, affecting approximately 25% of individuals between episodes BD [14]. Patients with UD may spend too much time in bed using sleep as an escape from troublesome symptoms such as anhedonia, lack of energy, and motivation. Similarly, patients with ADHD often find it hard to get out of bed because of initiation problems [15]. This may result in daytime inactivity and poor sleep hygiene [16]. Furthermore, poor sleep hygiene, e.g., exposure to blue light in the evening, is common in youth across mental disorders [10]. Apparently, real-life sleep problems are interwoven and complex [17]. Treatment for circadian rhythm disorders, hypersomnia, and insufficient sleep hygiene, as well as insomnia, is essential. Furthermore, interventions should be personalized to accommodate each patient´s unique sleep pattern [10].

Sleep problems are believed to play an important role in the onset, course, and treatment of UD, BD, and ADHD, with evidence suggesting a bidirectional relationship [6, 18–20]. Pharmacological sleep treatment is widespread but recommended for short-term use only due to the inherent risk of developing tolerance and addiction [21]. European and American guidelines recommend non-pharmacological treatment such as cognitive behavioral therapy for insomnia (CBT-I) as a first-choice treatment for chronic insomnia [21, 22]. CBT-I involves various interventions, including sleep restriction (limit time in bed to the actual sleep time); stimulus control method (strengthen the connection between bed and sleep); sleep hygiene education; relaxation training (reduce physiological arousal), and cognitive methods to address dysfunctional beliefs about sleep. CBT-I can be delivered in various treatment formats, including group, individual [23], and digital formats [24]. Meta-analyses found that CBT-I targeting insomnia with comorbid disorders had a medium to large effect on subjective sleep variables [25, 26].

The present intervention study is inspired by a transdiagnostic manual combining CBT-I with chronotherapy (treatment methods used to influence the circadian rhythm, such as bright light therapy and social rhythm therapy) in conjunction with motivational interviewing [27]. The manual provides transdiagnostic sleep interventions across a wide range of mental disorders [10]. Few studies have examined the effect of transdiagnostic sleep interventions. A positive effect on sleep parameters was shown in adolescents with various mental illnesses [28] and in 14 adolescents with ADHD [29]. Studies in adult outpatients with mental disorders and also midlife and older adults with serious mental illness documented a positive effect on sleep and circadian rhythm parameters and an improvement of psychiatric symptoms [30, 31]. However, despite extensive research on CBT-I, there is limited evidence of the effectiveness of combining CBT-I with chronotherapy as a transdiagnostic intervention in adult patients suffering from UD, BD, and ADHD. Therefore, more evidence is needed to adapt and incorporate the most effective interventions for sleep problems in mental healthcare services.

### Objectives {7}

The aim of the study is to investigate the efficacy of a transdiagnostic sleep intervention for patients with sleep problems comorbid to bipolar disorder, unipolar depression, or attention deficit disorders.

The primary hypothesis is that the transdiagnostic sleep intervention improves sleep quality compared with a control group receiving brief sleep hygiene education.

The secondary hypotheses are that a transdiagnostic sleep intervention increases subjective and objective sleep efficiency (SE), reduces sleep onset latency (SOL), wake after sleep onset (WASO), and nocturnal awakenings (NWAKE); and that it reduces the severity of insomnia, while increasing well-being, personal recovery, and work ability. Furthermore, participation in the intervention is expected to result in a reduction in the consumption of sleep medication compared with a control group receiving short sleep hygiene education.

### Trial design {8}

The study is a randomized controlled trial enrolling 88 outpatients with sleep problems (symptoms of chronic insomnia, circadian rhythm disorders, or hypersomnia) comorbid to BD, UD or ADHD. Patients are allocated to two parallel groups; an intervention group receiving six sessions of transdiagnostic sleep treatment or a control group receiving one session of sleep hygiene education. The allocation ratio is 1:1. After 6 weeks, the control group is offered the sleep intervention, but the data collected from this group will not be included in the present project.

## Methods: participants, interventions, and outcomes

### Study setting {9}

Patients are recruited from the outpatient unit entitled “Psykiatriens Hus,” organizationally located under the Department of Affective Disorders, Aarhus University Hospital Psychiatry, Central Denmark Region, Denmark. The patients referred to treatment for sleep problems are screened for the inclusion and exclusion criteria in connection with their first consultation. The referred patients receive treatment for their mental disorder at different out-patient’s clinics. Patients are generally referred to sleep treatment at “Psykiatriens Hus,” when they are relatively well treated and their mental disorder is stable.

### Eligibility criteria {10}

#### Inclusion criteria

We include patients with:

A diagnosis of F31 bipolar disorder, F32-33 unipolar depression, or F90 attention deficit disorder (ADHD, ADD) according to The International Classification of Diseases, tenth version (ICD-10).Age ≥ 18 yearsInsomnia Severity Index (ISI) ≥ 14 (corresponding to the sleep problem/insomnia threshold)

Sleep problems for 3 months: at least one of the following three times a week or more:SOL ≥ 30 minWASO ≥ 30 minTotal sleep time ≥ 11 h per dayDisplaced circadian rhythm; sleeps earlier than 8 pm or later than 02amIrregular circadian rhythm: bedtime varies ≥ 3 h throughout the week.

#### Exclusion criteria

Acutely increased suicide risk (the Central Denmark Regions guideline on assessment of suicide risk)Active substance abuse (F10–19)The sleep problem in the individual can be attributed to inadequate treatment of physical diseases affecting sleep, e.g., chronic pain condition (documented in the patients’ electronic journal)Unstable social situation (does not have a permanent residence)Shift work (≥ 2 times a week for the past 2 months)Pregnancy and breast-feedingParticipation in other psychiatric research interventions during the intervention period.

Symptoms of chronic insomnia disorder is defined as difficulties initiating or maintaining sleep or early morning awakenings for at least three months [32]. Standard criteria are defined as SOL or WASO for more than 30 min three times a week or more [33]. Symptoms of circadian rhythm sleep–wake disorders include delayed sleep phase disorder characterized by a sleep pattern delayed by more than 2 h compared to the socially acceptable bedtime and circadian sleep–wake disorder not otherwise specified, e.g., an irregular sleep–wake pattern [32]. For practical reasons, we define displaced circadian rhythm as sleeps earlier than 8 P.M. or later than 02 A.M. and the irregular sleep–wake pattern as a bedtime variability > 3 h. Both definitions are inspired by a study protocol by Harvey et al. [17]. Patients suffering from symptoms of hypersomnia associated with a psychiatric disorder experience excessive nocturnal sleep, daytime sleepiness, poor sleep quality not better explained by other disorders, or medication for more than 3 months [32]. No specific sleep duration is indicated for hypersomnia. In a study protocol by Harvey et al., a sleep length of 9 h was applied [17]. However, in young patients, a sleep length of 9 h is not unusual and we have therefore chosen a duration of 11 h to describe hypersomnia. The included patients are expected to fulfill the criteria of at least one of the following sleep disorders according to ICD-10; F51.05 Insomnia due to other mental disorder, F51.0 Nonorganic insomnia, F51.1 Nonorganic hypersomnia, F51.2 Nonorganic disorder of the sleep–wake schedule.

### Who will take informed consent? {26a}

Informed consent will be obtained from all patients before participation in the study. Patients are recruited through their primary contact nurse, doctor, or psychologist, who provide brief oral and written information about the research project. Furthermore, the primary contact person will obtain the patient's approval for establishing contact between the patient and a project member for a meeting where more thorough information will be given; patients are informed about their right to bring a companion or relative to this meeting. After the meeting, patients will be offered a 1–2-day reflection period before deciding whether to participate in the project or not. Hereafter, informed oral and written consent are obtained. Participation is voluntary, and patients may choose to withdraw from the project at any time. The patients will not receive any payment for participating in the study.

### Additional consent provisions for collection and use of participant data and biological specimens {26b}

Not applicable as no additional content is needed in this study.

### Interventions

#### Explanation for the choice of comparators {6b}

Patients in the control group receive individual sleep hygiene education consisting of a single session presenting the “10 Tips for Better Sleep” (see Additional file 1). They receive a flyer containing advice on how to promote good sleep practices and must work independently with these tips for the next 6 weeks while waiting for transdiagnostic sleep treatment. As a stand-alone intervention, sleep hygiene education has shown no effect on insomnia [34] and it is therefore chosen as the intervention given in the control group. Thus the intervention can be considered a sham treatment. However, sleep hygiene education is also often treatment as usual for this patient group.

#### Intervention description {11a}

The intervention group receives transdiagnostic sleep treatment consisting of six individual sessions lasting 60 min each in the course of 6 weeks. The sessions are conducted by a team of nurses, a physiotherapist, an occupational therapist, and a psychologist. These professionals have undergone a minimum of a two-day intensive theoretic sleep course to enhance their knowledge and skills in the field of sleep. Subsequently, they have received peer-to-peer training. Training and supervision are provided by the first and second authors of this paper.

The sessions have the following contents:Assessment and introduction to the sleep diary. The items from the sleep diary are similar to those of the consensus sleep diary [35]Sleep restriction, sleep compression, stimulus-control, or phase advance. Setting goals [10]Education about normal sleep, sleep problems, and circadian rhythmCognitive techniques (e.g., behavioral experiments) [10]Introduction to relaxation training (e.g., progressive muscle relaxation) [36]Follow-up on goals and plan for preventing sleep problem relapse

### Criteria for discontinuing or modifying allocated interventions {11b}

The allocated intervention will be discontinued on the patient’s request, and patients may withdraw from the study for any reason. The investigators have the discretion to withdraw patients from the study if their mental disorder is deteriorating, e.g., if they experience a manic episode, are at an acutely increased suicide risk, or if they are hospitalized for any reason.

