### Assignment of interventions: blinding

#### Who will be blinded {17a}

Blinding of allocation is not possible because of the nature of the intervention.

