### Data collection and management

#### Plans for assessment and collection of outcomes {18a}

Patients who discontinue study participation + / − 7 days from the planned follow-up at 2 or 6 weeks will be asked whether they wish to complete the questionnaires when they return the actigraph. The PSQI and ISI questionnaires will be prioritized.

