#### Plans to promote participant retention and complete follow-up {18b}

Patients who deviate from intervention protocols due to, e.g., illness, are asked to complete the questionnaires as soon as possible. We offer to do this with the patients by phone, at a home visit or virtually based on the patient’s preference. We also allow a flexibility of + / − of 7 days from the planned follow-up visits.

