### Statistical methods

#### Statistical methods for primary and secondary outcomes {20a}

Demographic and clinical data used to compare the intervention and control group will be analyzed using descriptive statistics. Categorical variables will be reported using proportions, whereas means and standard deviations will be reported for continuous variables. Fisher’s exact test and Student’s *t*-test are applied to test for the difference between the intervention and control group for categorical and continuous variables. The intent-to-treat method will be used to examine if a significant change in the ISI and PSQI total scores from baseline to 6 weeks can be established.

To compare the differences in measurements between the intervention and control group over time, we will apply a linear mixed effects (LME) model, which is recommended for longitudinal data with missingness [45]. The “maximum likelihood estimation” assuming “missing at random” for data is used to examine the primary and secondary continuous objectives. The fixed components of the model are gender, age, time variable (1: baseline, 2: 2 weeks, 3: 6 weeks), type of treatment (1: intervention group, 2: control group), and the interaction between the time variable and the type of treatment. Means, standard deviation, 95% confidence interval, power magnitude, and the average reduction over time and *p*-value for reduction in the primary and secondary outcomes will be calculated from the model. All statistical analyses will be performed using Stata version 15., R-Studio, or SPSS version 20.0.

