#### Methods in analysis to handle protocol non-adherence and any statistical methods to handle missing data {20c}

The intent-to-treat method will be used in conjunction with a LME model, which is recommended for longitudinal data with missingness.

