#### Adverse event reporting and harms {22}

Patients in the intervention group will be assessed for adverse events at weeks 2 and 6. All cases of serious adverse events will be reported to the Danish Scientific Ethics Committee.

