## Discussion

The strengths of the study are the use of both subjective and objective data. Furthermore, we investigate patients´ daytime functioning, which is important because sleep problems influence quality of life around the clock. Results from this trial will contribute to knowledge on the effect of the intervention and pave the way for implementing the most effective sleep problem interventions in mental healthcare services. However, the study also has some limitations. The PSQI questionnaire is a retrospective 30-day instrument used for inclusion at the first consultation. However, we also use it for measuring short-term, i.e., 2-week, effects. This results in an interval of only 14 days between assessments at baseline and week 2. Therefore, the answers obtained in week two are biased by baseline answers and comparison may be difficult. Perhaps it would have been appropriate to delay this second data collection, but because of the short 6-week study period, the second data collection would then be placed too late in relation to the last time point.

We have no outcomes related to mental disorders, which could have strengthened the design as the relationship between, e.g., insomnia and depression has been described as bidirectional [46]. Two meta-analyses have concluded that in patients with depression and comorbid insomnia, treatment with CBT-I may lead to an improved depression outcome with a medium-to-large effect size [25, 26]. However, the present study enrolls patients with depressive disorder, bipolar disorder, and attention deficit disorder. Therefore, psychopathology outcomes for each patient group would be needed. For this, we would need larger subgroups. Another option would be to assess general psychiatric symptoms across diagnoses [10], but this would not give answers as to whether diagnostically specific symptoms were reduced. Instead, we have chosen to describe day-time functioning and general well-being with other questionnaires.

Patients in the two groups do not have comparable treatment contacts with the research team. As illustrated in Fig. 1, the intervention group had six visits during the study period and the control group had only three. This may potentially cause improvement due to non-specific treatment factors in the intervention group.

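### Investigators who know the allocation may withdraw deteriorating patients from the study itself, and no stated rule clearly secures a week-6 PSQI for those withdrawn before day 35

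*Protocol article*

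**What the plan says.** All references are to the protocol article.

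- **Withdrawal, {11b}.** "The investigators have the discretion to withdraw patients from the study if their mental disorder is deteriorating, e.g., if they experience a manic episode". The sentence adds acutely raised suicide risk and admission to hospital for any cause. Stopping the intervention alone is mentioned only for the patient's own request.
- **Blinding, {16b}, {17a} and {17b}.** The investigator learns the allocation at randomisation. "Blinding of allocation is not possible because of the nature of the intervention". Only the data analysis is blinded.
- **Patients who leave the study, {18a}.** Those who leave within 7 days either side "from the planned follow-up at 2 or 6 weeks will be asked whether they wish to complete the questionnaires", at the time they hand back the actigraph. PSQI and ISI have priority.
- **Patients who deviate from the intervention, {18b}.** "Patients who deviate from intervention protocols due to, e.g., illness, are asked to complete the questionnaires as soon as possible". Telephone, home and virtual contact are offered, and visits may move by 7 days.
- **Analysis, {20a} and {20c}.** "The intent-to-treat method will be used in conjunction with a LME model", fitted by maximum likelihood under missing at random. "The fixed components of the model are gender, age, time variable", treatment, and the interaction of time with treatment.
- **Mental state, Discussion.** "We have no outcomes related to mental disorders".

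**The concern.** The section is headed as a rule on discontinuing or modifying the intervention, yet for a patient who worsens its stated action is removal from the study. Safety may require stopping sleep restriction or a phase shift. It does not require giving up the week-6 questionnaire.

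An intent-to-treat comparison needs the week-6 PSQI from every randomised patient as far as it can be had. Here the stated rules themselves create gaps, by an unblinded and discretionary decision tied to the patient's worsening. The mixed model predicts the missing value from arm, age, gender and the PSQI values already seen. Psychiatric deterioration is not in the model and is not measured as an outcome. Worsening that starts after week 2 is therefore invisible to the analysis, and no later analysis plan can recover a questionnaire that was never requested.

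**Working it through.** **1. Which withdrawals leave a week-6 PSQI**

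The visits are at day 14 and day 42, and the window is 7 days. So 14 − 7 = 7, 14 + 7 = 21 and 42 − 7 = 35.

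| Withdrawn on day | Asked under {18a} | Route to week-6 PSQI |
|---|---|---|
| 1–6 | nothing | none stated |
| 7–21 | questionnaires when the actigraph is returned | none stated; at most a week-2 value |
| 22–34 | nothing | none stated |
| 35–42 | questionnaires when the actigraph is returned | yes |

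{18b} does not clearly fill the gap. It concerns patients who depart from the intervention, and prompt completion does not give a week-6 value for someone withdrawn on day 25.

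**2. The planned effect, used as the yardstick**

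From {14}: effect 0.67 SD, power 0.80, significance level 0.05 (two-sided assumed), 25% dropout. The normal approximation gives n = 2 × ((1.96 + 0.842)/0.67)² = 34.97, so 35 per group, and 35 × 1.25 = 43.75, so 44. This matches the stated 44 per group. The fix below does not change it.

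**3. Size of a possible bias**

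The documents give no withdrawal rate by arm or reason, so these inputs are assumptions. Let pI and pC be the shares withdrawn in the intervention and control arms, and d the amount (in SD) by which withdrawn patients end worse than the model predicts. The bias in the estimated benefit is (pI − pC) × d; a positive value favours the intervention.

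| pI v pC | d = 0.5 | d = 1.0 |
|---|---|---|
| 10% v 5% | +0.025 | +0.05 |
| 15% v 5% | +0.05 | +0.10 |
| 5% v 5% | 0 | 0 |
| 5% v 10% | −0.025 | −0.05 |
| 5% v 15% | −0.05 | −0.10 |

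With 44 per arm, 5 points is 2.2 patients and 10 points is 4.4. Against 0.67, the range 0.025 to 0.10 is 3.7% to 14.9%.

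**4. How much the mixed model recovers**

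Assume a correlation of 0.5 between any two visits. The week-2 value then has weight 0.5/(1 + 0.5) = 1/3 in predicting week 6, given baseline. Suppose the intervention arm has 2 more withdrawals than control, each 1 SD worse:

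- None of the worsening visible at week 2: 2/44 × 1 = 0.045 SD.
- Half of it visible at week 2: 2/44 × (1 − 0.5 × 1/3) = 0.038 SD.

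**5. Effect on the error rate**

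For the first of these cases, with 7 other week-6 losses per arm also assumed, the standard error is 0.229. The shift is 0.045/0.229 = 0.20. With no true effect, the chance of a result in favour of the intervention is 1 − Φ(1.96 − 0.20) = 0.039 and in the other direction 0.015. The two-sided total is about 0.054 against 0.05. With 4 excess withdrawals (bias 0.091, standard error 0.231) the total is about 0.068.

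**The case against.** **The two follow-up rules complement each other, and withdrawal is not mandatory.** An investigator may stop the sessions and follow the patient under {18b}. That is possible, and the number of full withdrawals may be small: patients are generally referred when stable ({9}) and acute suicide risk is an exclusion ({10}). But nothing directs the investigator to that choice, and {18b} is not tied to week 6.

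**The article condenses a longer protocol that is not shown.** This is a good answer to any demand for a log of withdrawal reasons or a sensitivity analysis, and neither is held against the plan here. It does not answer a rule that the article states and that limits whom to ask.

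**A reader might infer that the bias favours the intervention.** That arm has six visits against three (Discussion), and only there are adverse events planned to be assessed: "Patients in the intervention group will be assessed for adverse events at weeks 2 and 6". The documents do not support this reading. Patients are treated for their mental disorder at other clinics ({9}), and sessions with the contact nurse go on as concomitant care ({11d}). Mania, suicide risk and admission would be noticed there in either arm. The adverse-event checks fall at weeks 2 and 6, when a PSQI is due anyway. Controls could deteriorate more, and a manic patient may report fewer sleep complaints.

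**A reader might also take the day count as the extent of the loss.** Days 1 to 34 are 34 of 42, or 81%, but that is a share of the calendar, not of patients or of missing data. Likewise, a false-positive rate of 0.039 against 0.025 is one tail only, under assumed counts.

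**Conclusion.** The point holds as a minor one. Followed as written, {11b} and {18a} leave patients withdrawn before day 35 without a clear route to the week-6 PSQI, for reasons linked to worsening, while {20a} and {20c} promise intent-to-treat under missing at random. The model repairs this only as far as earlier PSQI values already show the decline.

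Neither the direction nor the size of a bias can be read from the documents. About 0.03 to 0.10 SD either way rests on two assumptions: withdrawal shares that differ by 5 to 10 percentage points, and outcomes 0.5 to 1 SD worse than predicted. With equal shares and equal outcomes it is zero. The case for change is that the loss is avoidable, not that the result is shown to be distorted.

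**What to change.** - **{11b}:** replace withdrawal from the study by the investigator with discontinuation of the allocated intervention. The patient stays in the study and is asked for PSQI and ISI at week 6, unless consent is withdrawn.
- **{18a}:** drop the 7-day limit and use the telephone, home or virtual contact that {18b} already offers.
- **Separate harms point, {22}:** assess adverse events at weeks 2 and 6 in both arms. Control patients already complete questionnaires at personal visits in those weeks ({19}), so no visit is added.

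Cost: a formal amendment with ethics approval ({25}) in a trial that began recruiting in May 2022, and one short contact for each discontinued patient. The sample size is unchanged. Some manic, suicidal or hospitalised patients will still be unable to answer, so the gap shrinks but does not close.
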